## Abstract

**Background:**

Opioids are a key component of pain management among patients with metastatic cancer pain. However, the evidence base available to guide opioid-related decision-making in individuals with advanced cancer is limited. Patients with advanced cancer or cancer that is unlikely to be cured frequently experience pain. Opioids are a key component of pain management among patients with metastatic cancer pain. Many individuals with advanced cancer are now living long enough to experience opioid-related harm. Emerging evidence from chronic noncancer pain literature suggests that longer-term opioid therapy may have limited benefits for pain and function, and opioid-related harms are also a major concern. However, whether these benefits and harms of opioids apply to patients with cancer-related pain is unknown.

**Objective:**

This manuscript outlines the protocol for the “Opioid Therapy for Pain in Individuals With Metastatic Cancer: The Benefits, Harms, and Stakeholder Perspectives (BEST) Study.” The study aims to better understand opioid decision-making in patients with advanced cancer, along with opioid benefits and harms, through prospective examination of patients’ pain experiences and opioid side effects and understanding the decision-making by patients, care partners, and clinicians.

**Methods:**

This is a multicenter, prospective cohort study that aims to enroll 630 patients with advanced cancer, 20 care partners, and 20 clinicians (670 total participants). Patient participants must have an advanced solid cancer diagnosis, defined by the American Cancer Society as cancer that is unlikely to be cured. We will recruit patient participants within 12 weeks after diagnosis so that we can understand opioid benefits, harms, and perspectives on opioid decision-making throughout the course of their advanced cancer (up to 2 years). We will also specifically elicit information regarding long-term opioid use (ie, opioids for ≥90 consecutive days) and exclude patients on long-term opioid therapy before an advanced cancer diagnosis. Lived-experience perspectives related to opioid use in those with advanced cancer will be captured by qualitative interviews with a subset of patients, clinicians, and care partners. Our data collection will be grounded in a behavioral decision research approach that will allow us to develop future interventions to inform opioid-related decision-making for patients with metastatic cancer.

**Results:**

Data collection began in October 2022 and is anticipated to end by November 2024.

**Conclusions:**

Upon successful execution of our study protocol, we anticipate the development of a comprehensive evidence base on opioid therapy in individuals with advanced cancer guided by the behavioral decision research framework. The information gained from this study will be used to guide interventions to facilitate opioid decisions among patients, clinicians, and care partners. Given the limited evidence base about opioid therapy in people with cancer, we envision this study will have significant real-world implications for cancer-related pain management and opioid-related clinical decision-making.

**International Registered Report Identifier (IRRID):**

DERR1-10.2196/54953

## Introduction

Patients with advanced cancer or cancer that is unlikely to be cured frequently experience pain [1,2]. Although the overall prevalence of pain and pain severity related to cancer appear to be decreasing, 40% of patients with cancer experienced pain during and up to 3 months after cancer treatment [1,3,4]. When stratified by cancer severity, patients with more advanced disease have higher rates of pain: up to 66%, compared to 39% for patients with localized or curative disease [4]. Although patients with any cancer can experience pain, those with breast, lung, head, and neck cancer experience pain most often [5]. Under- and untreated pain in individuals with cancer is associated with a variety of adverse health consequences, including functional limitations (eg, inability to work), suboptimal health behaviors (eg, reduced physical activity), emotional distress, social isolation, high health care use (eg, emergency department and inpatient admissions), and earlier death [6-9].

Opioids are a key component of pain management among patients with metastatic cancer pain [10]. Although rates of opioid prescribing in advanced cancer have not been well described, people with advanced cancer are prescribed long-term opioid therapy (ie, opioid prescription for at least 90 consecutive days) more often than people with limited-stage disease (66% vs 40%) [11]. A recent study using data from the National Survey on Drug Use and Health found that approximately half of cancer survivors with a recent diagnosis (within 12 months of the National Survey on Drug Use and Health survey) were prescribed an opioid during that year (54%) [12]. National guidelines from the American Society of Clinical Oncology [10] and the National Comprehensive Cancer Network [13] support opioids as a cornerstone of pain management for individuals with advanced cancer, suggesting that the benefits of opioid use outweigh the harms for this patient group.

However, many individuals with advanced cancer are now living long enough to experience opioid-related harm. Indeed, some advanced cancers are considered chronic diseases as patients are surviving longer due to improvements in cancer treatments [14]. For example, the median survival of individuals with metastatic breast cancer in a large national cohort of patients with breast cancer in France was 37 months [15], which has increased steadily over the previous decades [16]. Approximately one-third of individuals with metastatic breast cancer [17] or metastatic prostate cancer [18] survive for at least 5 years. This presents a complex clinical context for treating cancer-related pain with opioids, increasing the need to balance opioid-related benefits and harms.

Emerging evidence from the chronic noncancer pain literature suggests longer-term opioid therapy may have limited benefits for pain and function. For example, a recent meta-analysis of randomized controlled trials of opioids versus placebo for chronic (>3 month) “noncancer” pain observed a small improvement in pain of 0.69 (95% CI 0.56-0.82) on a scale of 0-10 that was less than the prespecified minimum clinically important difference of 1 [19]. Other systematic reviews and meta-analyses have yielded similar findings, including a lack of functional improvement with opioid therapy over placebo [20,21]. Analogous data do not yet exist for patients with advanced cancer; given the unique features of cancer pain and the commonly concurrent noncancer pain experienced by patients with cancer, it is important to better understand pain and pain management in persons with advanced cancer.

Opioid-related harms are also a major concern among people prescribed opioids. In one meta-analysis of 26 studies, 23% of participants decided to discontinue opioids due to side effects (eg, nausea and dizziness) [22]. In the general population, long-term opioid therapy is also associated with more serious harms; 21% to 29% develop opioid misuse, and 8% to 12% may progress to an opioid use disorder. Although more rare, opioid overdoses can occur (256 per 100,000 person-years among people recently prescribed opioids vs 36 per 100,000 years among those not prescribed opioids) [23,24]. In studies of noncancer pain, opioid-related harms are consistently related to both ingestion of high-dose opioids (ie, >90 mg morphine equivalents) and coprescription of sedating medications (benzodiazepines and gabapentin) [25-28]. People with cancer are more likely to be represented in the high-dose opioid groups and frequently experience polypharmacy [29,30]. However, whether these benefits and harms of opioids apply to patients with cancer-related pain is unknown.

This manuscript describes the study protocol for “Opioid Therapy for Pain in Individuals With Metastatic Cancer: The Benefits, Harms, and Stakeholder Perspectives (BEST) Study.” The study aims to better understand opioid decision-making in patients with advanced cancer, along with opioid benefits and harms, through prospective examination of patients’ pain experiences and opioid side effects and understanding the decision-making by patients, care partners, and clinicians.

## Methods

### Study Design

This is a multicenter, prospective cohort study that aims to enroll 630 patients with advanced cancer, 20 care partners, and 20 clinicians (670 total participants). The data collection is underway at 4 clinical sites. Site selection considered geographic diversity (Northeast, mid-Atlantic, West, and Southeast), the balance of urban versus rural patients, sufficient patient volume to reach the enrollment goal, and the ability to recruit based on previous success in cancer studies. Given well-established health disparities in cancer pain and its treatment, we selected sites that demonstrated a track record of successful recruitment of Black and Hispanic patient participants [31]. None of the chosen sites have opioid stewardship committees or programs, which could have the unintended consequence of limiting opioid prescribing [32]. Additionally, we conducted a comprehensive review of state opioid laws in preparation for the study [33], with most states specifying blanket cancer exemption for any opioid limitation, such as dose or limited day supply.

### Participants

Patient participants must have an advanced solid cancer diagnosis, defined by the American Cancer Society as cancer that is unlikely to be cured [2]. An advanced cancer diagnosis can include patients who have distant metastases or a recurrence. Patient participants must be their own decision maker as determined by the electronic medical record (EMR) and enroll within 12 weeks of their advanced cancer diagnosis date. The research team will confirm an advanced cancer diagnosis using medical record documentation of pathology results or radiology and oncology documentation. We will recruit patient participants early after diagnosis so that we can understand opioid benefits, harms, and perspectives on opioid decision-making throughout the course of their advanced cancer (up to 2 years). Lived-experience perspectives related to opioid use in those with advanced cancer will be captured by qualitative interviews with a subset of enrolled patients, clinicians, and care partners.

We will specifically elicit information regarding long-term opioid use (ie, opioids for ≥90 consecutive days) and exclude patients on long-term opioid therapy before an advanced cancer diagnosis. Consistent with previous studies, we confirm opioid use in the medical record and will ask patient participants, “Did you take a strong prescription pain medication known as an opioid or narcotic for at least 90 days in a row during the past year? Examples of opioids include oxycodone, hydrocodone, hydromorphone, morphine, fentanyl, buprenorphine, methadone, and combination products such as oxycodone/acetaminophen.” This question is consistent with other commonly used research definitions of long-term or chronic opioid therapy [34,35]. Notably, this long-term opioid use definition also excludes individuals who are receiving methadone or buprenorphine/naloxone (suboxone) for the treatment of opioid use disorder, as the potential benefits and harms of opioid therapy in this population are unique and merit separate investigation [36]. This will allow us to understand the benefits, risk factors for harm, and perspectives on opioid decision-making when a patient with newly diagnosed advanced cancer begins an opioid or continues a newly initiated opioid.

From the larger cohort, we will recruit 40 patient participants with advanced cancer—20 who are prescribed opioids at the time of enrollment and 20 who are not. From that sample of 40 patients, we will aim to obtain consent from care partners of at least 20 patients and clinicians of at least 20 patients.

We will exclude individuals younger than 18 years of age, prisoners, pregnant people, and patients currently enrolled in hospice at the time of recruitment from the study. Patient participants do not need to report pain at the time of diagnosis since pain can occur at any point in the cancer trajectory. By including patient participants without pain at the time of diagnosis of metastatic disease, the study has the added benefit of describing the natural history of pain in patients with metastatic cancer for 2 years after diagnosis, filling an existing literature gap [3]. Patients who meet advanced cancer eligibility criteria will be recruited irrespective of their predicted prognosis, due to the inherent challenges of predicting prognosis [37,38].

For qualitative interviews, care partner participants must be a spouse, partner, child, relative, or friend who helps the patient with activities of daily living and health care needs at home, consistent with the National Cancer Institute definition of family caregivers [39]. Clinician participants will be physicians or advanced practice clinicians caring for a patient participant who has opioid prescribing authority and is willing to participate in a qualitative interview.

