#### Assessments

Once patients have consented and enrolled in the study, data collection will include patient-reported outcomes (PROs), chart reviews, and interviews. Table 1 provides an overview of the study procedures and time frame.

**Table 1 table1:** Schedule of research activities.

Study stage	Screening and enrollment	Follow-up			
	Within 12 weeks of the date of diagnosis	Weekly after baseline	Monthly after baseline	Quarterly after baseline	Semiannually after baseline
Prescreening	✓				
Consent, screening, and contact information	✓				
Demographics and medical history	✓				
Baseline and demographics	✓				
Weekly 3-questions pain assessment: pain severity and inference		✓			
Monthly PRO^a^ assessment: mood, substance use, symptoms, and opioid misuse (Carey 2-year index)			✓		
Chart reviews: substance use, opioid misuse, and opioid overdose				✓	
Patient calls and chart review: Opioid prescription or dose, benzodiazepine prescription, over or under consumption of opioids					✓
TAPS^b^: substance use and opioid use disorder				✓	
Patient participants, care partners, and clinician interviews				✓	

^a^PRO: patient-reported outcome.

^b^TAPS: Tobacco, Alcohol, Prescription Medication, and Other Substance Use Tool.

Study staff will confirm patient demographics and cancer type from the medical record. Sites will use a chart abstraction tool to gather medication-related data every 6 months. Opioid dose will also be assessed through self-report by reading back the dose and instructions on the opioid bottle and confirmed in the EMR. Patient participants will consent to receiving a phone call from the study staff for pill counts during the latter part of the month of their prescriptions every 3 months.

Patient participants will complete baseline assessments and PROs electronically using REDCap, over the phone, or during clinic visits through a tablet by the study staff. If patient participants are unable to complete PROs, care partners will be permitted to complete the PRO assessments on behalf of the patient participants. We acknowledge that based on systematic reviews in oncology, there may be differences in patient-proxy reports, with proxies having a more negative view of the patient’s well-being [47].

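### The long-term opioid screening question counts days after diagnosis, so it can screen out patients whom the stated exclusion, anchored at diagnosis, would keep

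*Protocol article*

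**What the plan says.** The Participants section of the protocol article states the criterion relative to diagnosis: the study will "exclude patients on long-term opioid therapy before an advanced cancer diagnosis". It defines long-term use as at least 90 consecutive days.

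The same paragraph quotes the question put to patients, which asks about opioid use "for at least 90 days in a row during the past year". The question does not mention the diagnosis date. The paragraph then refers to this as the definition of long-term use and says that it excludes people.

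Patients must "enroll within 12 weeks of their advanced cancer diagnosis date". Table 1 in the Assessments section places screening and enrolment in the same window ("Within 12 weeks of the date of diagnosis").

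The article mentions a second source, "we confirm opioid use in the medical record", but gives no reference date for it. The stated purpose of the criterion is to study a newly diagnosed patient who "begins an opioid or continues a newly initiated opioid".

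**The concern.** The rule and the question that implements it use different reference dates. The rule looks back from diagnosis. The question looks back from the day it is asked, which may be up to 12 weeks later. Any opioid days between diagnosis and screening lengthen the run that the question counts, although the rule gives them no weight.

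Two things are at stake. First, eligibility comes to depend on when staff reach the patient, which should have no bearing on whether long-term use preceded diagnosis. Second, the patients who can be wrongly caught are continuous users whose opioid began in the weeks before diagnosis, plausibly for the symptoms that led to it. Some of them are continuing a newly initiated opioid and so belong to the population that the article says it wants. Their removal would be selective on opioid exposure and continuity of use, and probably on early pain. Adjusting for baseline pain in the Aim 1 model cannot bring back patients who were never enrolled.

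**Working it through.** The article states no figure to reproduce, so the check is a day count.

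**Inputs** (all from the Participants section; the window is repeated in Table 1)
- Duration that defines long-term use: 90 consecutive days.
- Latest enrolment: 12 weeks × 7 = 84 days after diagnosis.
- Look-back of the question: one year from the day it is asked.

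**Formula.** Take a patient who starts an opioid *s* days before diagnosis, uses it without a break, and is screened *d* days after diagnosis (0 ≤ *d* ≤ 84).
- Run length at screening = *s* + *d*.
- Question as worded: yes when *s* + *d* ≥ 90, that is *s* ≥ 90 − *d*.
- Rule as stated: excluded when *s* ≥ 90, whatever *d* is.

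The patients wrongly caught are those with 90 − *d* ≤ *s* < 90.

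| Screened at | *d* (days) | Smallest *s* that gives a yes (90 − *d*) | Smallest *s* under the stated rule |
|---|---|---|---|
| Week 0 | 0 | 90 | 90 |
| Week 2 | 14 | 76 | 90 |
| Week 4 | 28 | 62 | 90 |
| Week 6 | 42 | 48 | 90 |
| Week 8 | 56 | 34 | 90 |
| Week 10 | 70 | 20 | 90 |
| Week 12 | 84 | 6 | 90 |

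If both end days are counted, each entry in the third column falls by one.

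**Example.** Two patients each start 30 days before diagnosis. Screened at week 4, the run is 30 + 28 = 58 days and the patient is eligible. Screened at week 10, it is 30 + 70 = 100 days and the patient is screened out. Under the stated rule both are eligible.

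**Start on or after diagnosis.** Here *s* ≤ 0, so the run is at most 84 days. It can never reach 90 within the window.

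**How often a given patient would be caught.** The article gives no distribution of enrolment times. As an assumption only, let all 85 days from 0 to 84 be equally likely. The number of days on which *s* + *d* ≥ 90 is then:
- *s* = 6: 1 of 85 (1%)
- *s* = 14: 9 of 85 (11%)
- *s* = 30: 25 of 85 (29%)
- *s* = 60: 55 of 85 (65%)

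These are chances for a patient with a given start date. They are not the share of the cohort affected, which would also need the distribution of opioid start dates.

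**Look-back.** At week 12 the question reaches only 365 − 84 = 281 days before diagnosis, so the pre-diagnosis period it covers also changes with enrolment timing.

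**The case against.** The strongest reply is that the governing rule is already anchored at diagnosis and the question is only one of two tools. The record check is named alongside it, the Recruitment section has a coordinator review the record to verify eligibility, and the diagnosis date must be known to apply the 12-week limit. Staff therefore have what they need to overrule a yes, and a screening manual may tell them to. This stands in part: a yes can be corrected. But the article does not say that a dated start overrides the answer, and it treats the question as the definition that excludes. The conflict is between two things it states, not a detail it omits.

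It can also be said that anyone wrongly caught already has 90 days of use at enrolment, and that leaving such users out is defensible. It may be, but that would be a criterion relative to enrolment, which is not the one stated.

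Two stronger readings are tempting and are not supported:
- A reader might infer that the question generally removes patients whose opioid began days before diagnosis. That is literal only near week 12. Earlier screening requires weeks of prior use, only unbroken use counts, and the article says recruitment is early after diagnosis, where the effect is smallest.
- A reader might infer that Aims 1 and 2 lose power. Recruitment continues to 630, Aim 1 uses current opioid prescription over repeated measurements, and its power scenarios span 30% to 70% prescribed opioids. Aim 2 assumes about 50%, and nothing shows that this share would move.

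**Conclusion.** The criterion and the screening question do not agree, and the disagreement can produce a wrong eligibility decision. The pre-diagnosis use that triggers a yes falls from 90 days at diagnosis to 6 days at the end of the enrolment window, when it should stay at 90. This assumes continuous use and a yes that is not corrected from dated records.

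The effect is confined to continuous users who started before diagnosis but fewer than 90 days before it, and it grows with later screening. How many patients that is cannot be computed from the article. The consequence is a possible selective loss of some patients continuing a newly initiated opioid; bias in the Aim 1 or Aim 2 estimates has not been demonstrated. The point should be corrected because the error is specific and re-anchoring is cheap.

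**What to change.** - Reconcile the question and the record check with the stated criterion. Ask about 90 consecutive days of use in the year before the patient's advanced cancer diagnosis date, with that date filled in, and have the record check use dated prescriptions against the same date.
- State that opioid days after diagnosis do not count toward the 90.
- If exclusion relative to enrolment was what the investigators intended, restate the criterion that way instead and revise the description of the target population to match.
- For patients already screened, report how many were excluded on this item, with their screening date and opioid start relative to diagnosis. Re-approach only those still within 12 weeks, since the others can no longer enrol.
- Record which wording each patient was screened under.

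The cost is a minor amendment, some chart work across the four sites, and a cohort screened under two wordings. The Results section expected recruitment to finish by November 2024. If it has closed, what remains is to report the exclusions on this item and describe the limitation.

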### Analytic Plan

#### Aim 1: Data Analysis

This analysis will draw from all patient participants, regardless of whether they are prescribed opioids, so we can compare those who are with those who are not prescribed opioids. We will estimate differences in pain severity and interference between patients treated with opioids versus patients not treated with opioids using linear mixed-effects models, which will allow us to (1) account for repeated measures over time for each patient and (2) adjust for potential confounders. In the linear mixed-effects models, the dependent variables will be based on the PEG: pain severity (first question is a continuous 0-10 value) and pain interference (mean of 3 PEG items) at each time point. Current opioid prescription, baseline pain severity or interference, and other confounders (ie, factors statistically associated with the exposure and outcome) will be included as fixed effects, while the subject will be included as a random effect.

#### Power Calculation for Aim 1

Power calculations were performed by simulation to allow a range of parameters to vary in all scenarios. Unlike a randomized trial, in this study we will not have control over the ratio of patients allocated to the 2 comparison groups (eg, there will not be precisely a 1:1 ratio of patients prescribed opioids vs patients not prescribed opioids for comparison). Scenarios were considered where the proportion of patients prescribed opioids was allowed to vary from 30% up to 70%, all assuming a mean baseline PEG of 6 in the patients not prescribed opioids, a reduction in the PEG of 1 point for patients that are prescribed opioids, and a common standard deviation in PEG scores of 2 points [51]. All scenarios considered had at least 90% power to detect a difference of 1 point between groups with a total sample size of 630 patients (allowing for 30%-70% of the population to be prescribe opioids, meaning that with a range of 189 up to 441 patients prescribed opioids during the study period, there is ample power to detect differences between groups). All scenarios had at least 99% power to detect a 2-point difference on the PEG. We acknowledge that up to 40% of patients may drop out during the study due to the morbidity and mortality of patients in palliative care [58]. Data up until the point of attrition will be included in the analysis, and this has also been accounted for in our calculations.

#### Missing Data for Aim 1

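### The 90-day, pain-medication definition does not by itself exclude every patient receiving methadone or buprenorphine/naloxone for opioid use disorder, although the protocol says it does

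*Protocol article*

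**What the plan says.** The Participants section of the Protocol article defines "long-term opioid use (ie, opioids for ≥90 consecutive days" and says that the study will "exclude patients on long-term opioid therapy before an advanced cancer diagnosis". Two sources identify such use. One is a patient question about a "strong prescription pain medication known as an opioid or narcotic for at least 90 days in a row during the past year", followed by a list: "Examples of opioids include oxycodone, hydrocodone, hydromorphone, morphine, fentanyl, buprenorphine, methadone" and combination products. The other is the chart: "we confirm opioid use in the medical record". The section then states that "this long-term opioid use definition also excludes individuals who are receiving methadone or buprenorphine/naloxone (suboxone) for the treatment of opioid use disorder", because the protocol regards benefit and harm in these patients as different enough to need a study of their own.

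The remaining exclusions in that section are age under 18, imprisonment, pregnancy and current hospice enrollment. In Aim 1: Data Analysis, the model's fixed effects are "Current opioid prescription, baseline pain severity or interference, and other confounders". The analysis for hypothesis 2b is a Cox model for opioid misuse and use disorder, with history of substance use disorder as one of three predictors.

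**The concern.** The protocol names a group to be kept out and relies on the 90-day rule to do it. Receiving treatment for opioid use disorder and having taken an opioid for 90 consecutive days as pain medication are different conditions, so the second cannot be assumed to cover the first.

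Two analyses are exposed if such patients enter. In Aim 1 the exposure is a current opioid prescription with no limit by indication, so a drug given for opioid use disorder could be counted when estimating an effect on pain. In Aim 2b these patients would start follow-up with the predictor (substance use disorder history) and one of the outcome conditions (opioid use disorder) already present, so they are not at risk of a first occurrence.

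**Working it through.** The plan gives no figure to reproduce here. The check sets the claimed exclusion beside the rule that is meant to deliver it.

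**Inputs (Protocol article, Participants)**
- Group to be excluded: anyone receiving methadone or buprenorphine/naloxone for opioid use disorder, no duration stated.
- Rule: at least 90 consecutive days, before the advanced cancer diagnosis.
- Question: pain medication, 90 days in a row, past year; buprenorphine and methadone are among the examples.
- Second source: opioid use confirmed in the record, with no duration stated for that check.
- Enrollment: within 12 weeks of diagnosis.

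**Cases**
1. *Treated for 90 or more consecutive days before diagnosis.* Meets the rule. Both drugs are named in the question and the record is a second source. Largely captured.
2. *Recent start or interrupted treatment, with no run of 90 consecutive days.* Does not meet the rule, and no other listed criterion applies. Can pass. An interruption alone is not enough: any 90-day run within the past year still gives a yes to the question.
3. *Treatment started after diagnosis.* Longest possible duration at enrollment is 12 weeks x 7 days = 84 days, and 84 < 90. Such treatment also falls outside the part of the rule that looks before diagnosis. Can pass.
4. *Treated for 90 or more days, but the patient answers no because the drug is not taken for pain.* The answer is truthful on the wording of the question. Only the record check remains; if it misses the patient, the patient passes.

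The rule therefore covers established treatment (case 1) but not everyone receiving treatment (cases 2 and 3, and possibly 4).

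**Scale**
- Number of such patients: not given in the document.
- Aim 1: the power section considers 189 to 441 patients prescribed opioids. One patient is 1/441 = 0.2% to 1/189 = 0.5% of the exposed group.
- Aim 2b: opioid use disorder is expected in about 10% of 315, so 0.10 x 315 = 31.5 events. Only if a pre-existing case were scored as an event would one patient make up 1/31.5 = 3.2% of events. The document does not say that it would be.

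**The case against.** The strongest reply is that the exclusion and its reason are stated outright, without a time limit. Staff who find a recent prescription for opioid use disorder in the chart would have grounds to exclude the patient. The Recruitment section has coordinators review records to verify eligibility, and the article does not tie the record check to 90 days. The article is also a condensed account: a separate checklist item may exist in the full protocol. Much of this stands. It shows that the intent is clear and that practice may be better than the text. It does not make the stated inference correct, since the article names the long-term-use definition as the means of exclusion and that definition does not reach cases 2 and 3.

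Three stronger readings are tempting and not supported.
- A reader might infer that the definition fails altogether and that the whole group can enter. It does not fail for established treatment, since both drugs are named and the chart is checked.
- A reader might infer that the record check applies the same 90-day rule and so cannot catch recent starters. The article does not say so.
- A reader might infer that each admitted patient adds an event to Aim 2b. The section on missing data for Aim 2 counts the development of complications, which points to new occurrence, and nothing says that existing disorder is scored as an event.

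Patients with earlier opioid use disorder who are not on these drugs remain eligible. The baseline-status question in Aim 2b is therefore wider than this exclusion, and closing this gap does not settle it for them.

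**Conclusion.** The point holds in limited form. The stated rule does not deliver the full exclusion that the protocol attributes to it, and the two statements must be reconciled. The gap consists of patients without a 90-day run, patients who start after diagnosis, and patients whose no answer is not corrected by the record.

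The effect is probably small. With no count in the documents, neither the number of patients nor the bias can be estimated. The direction in Aim 2b is also open: scoring existing disorder as an event would push the association with substance use disorder history upward, while keeping such patients in the risk set as non-events would push it downward. The conclusion assumes that the eligibility text in the article is the operative rule. If the full protocol already has a separate criterion, only the article's wording needs correction.

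**What to change.** Make current receipt of methadone or buprenorphine, with or without naloxone, as treatment for opioid use disorder a separate exclusion of any duration. Check it with a question that asks about indication and with record review for the same item, and remove the claim that the 90-day definition covers it.

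Recruitment was expected to finish by November 2024, so the eligibility change may reach few or no further patients. The analysis side remains useful because follow-up runs to November 2026. For patients already enrolled, flag the indication at baseline from the record, do not count such a prescription as opioid exposure for pain in Aim 1, and leave these patients out of the Aim 2b risk set for opioid use disorder. Fix this rule before the analysis is run and report how many patients it affects.

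The cost is one eligibility line, one screening question, a small amount of retrospective flagging, and the loss of a few patients.
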